#### Voluntary Withdrawal of Participants

Participants are allowed to withdraw from the trial at any time, according to the informed consent form. Participants who do not formally withdraw from the trial but stop receiving intervention treatment or testing on their own, or are lost to follow-up, are considered to have withdrawn. The reasons for all participants who withdraw from the trial should be identified and documented to the extent possible.

### Sample Size

The sample size was calculated by the statistician of the Clinical Evaluation Center of Shanghai University of Traditional Chinese Medicine by the Power Analysis and Sample Size (PASS) 14 software. PFS is the primary endpoint. According to our previous study, the median PFS of the control group is expected to be 18 months and that of the intervention group is expected to be 23 months, with a recruitment duration of 18 months and a total duration of 30 months. The two groups were allocated in a ratio of 1:1. Given that *α* = 0.05, *β* = 0.20, considering that the average monthly censored rate is 1%, the total sample size is 314 cases, 157 cases in each group.

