## Introduction

Non-small cell lung cancer (NSCLC) is the leading cause of cancer death worldwide (Siegel et al., 2020). Epidermal growth factor receptor (EGFR) is the most common driver gene for NSCLC, and approximately 40% of NSCLC patients in Asian populations have EGFR mutations (Gelatti et al., 2019). The most common mutation types in EGFR include exon 19 deletion (Ex19del) and exon 21 Leu858Arg (L858R), often referred to as “classical” mutations (Gazdar, 2009), which account for about 85% of EGFR mutations (Harrison et al., 2020). In addition, 12%–34% of NSCLC patients with EGFR mutations have uncommon mutations (Yang et al., 2015; Castellanos et al., 2017; Robichaux et al., 2018), which include exon 20 insertion, exon 18 G791X, exon 20 S768I, and exon 21 L861Q mutations. However, evidence on the efficacy of treatment for patients with uncommon mutations is insufficient. First-generation epidermal growth factor receptor tyrosine kinase inhibitors (EGFR-TKIs), such as gefitinib (Fukuoka et al., 2011) and erlotinib (Rosell et al., 2012), significantly improve the prognosis of advanced NSCLC patients harboring EGFR-TKI-sensitizing mutations, mainly EGFR Ex19del and L858R, when compared with traditional platinum-based chemotherapy as first-line treatment. Despite initial responses, most patients develop acquired resistance to first-generation EGFR-TKIs, and the disease will progress within 9–11 months (Fukuoka et al., 2011; Rosell et al., 2012). Third-generation EGFR-TKIs such as osimertinib have been shown to delay disease progression and prolong survival time compared to gefitinib (Soria et al., 2018; Ramalingam et al., 2020). Despite this, acquired resistance to osimertinib develops over a median of 18.9 months, so optimizing the effect of osimertinib is critical to the long-term survival of NSCLC patients.

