Chinese herbal medicine (CHM) has been used in Chinese NSCLC patients treated with EGFR-TKIs for more than 10 years and has demonstrated its efficacy in delaying EGFR-TKI resistance and alleviating adverse effects in a number of clinical trials (Yang et al., 2018; Jiao et al., 2019; Tang et al., 2019). CHM contains several active compounds that interact with target proteins involved in EGFR-TKI resistance (Bing et al., 2018). Our previous multi-center, double-blind, placebo-controlled clinical trial (CATLA study) confirmed that the addition of CHM (Yiqi-Yangyin-Jiedu decoction, YYJD) to EGFR-TKI (gefitinib, erlotinib, or icotinib) significantly prolongs progression-free survival (PFS) and improves the quality of life (QoL) in NSCLC patients (Jiao et al., 2019). These trials mainly involve first-generation EGFR-TKIs. Osimertinib, as a third-generation EGFR-TKI, inhibits EGFR-sensitive mutations (Ex19del and L858R) like the first-generation EGFR-TKI. Given their similar mechanisms of action, it is reasonable to expect CHM to have clinical benefits for osimertinib as well.

The current study (CATLA-2) will determine whether the addition of CHM YYJD to third-generation EGFR-TKI osimertinib (O+YYJD) prolongs PFS compared with osimertinib plus placebo (O+placebo) in advanced NSCLC patients who have an activating EGFR mutation.

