As a complementary and alternative medicine, TCM is widely used in cancer treatment in China, which has shown the effects of reducing chemotherapy toxicity, enhancing tumor treatment response, improving quality of life, and prolonging survival (Zhang et al., 2018). In the CATLA study, we found that the combination of EGFR-TKIs (gefitinib, erlotinib, or icotinib) and CHM YYJD as first- and second-line therapy significantly prolonged PFS and ORR versus EGFR-TKIs alone. The median PFS was prolonged by 5 months as first-line treatment. At the same time, the side effects of EGFR-TKIs, including fatigue, loss of appetite, diarrhea, pruritus, and skin rash, were reduced (Jiao et al., 2019). Nowadays, the advantage of the third-generation EGFR-TKI, osimertinib, over the first-generation EGFR-TKI is that it overcomes the T790M resistance mutation and has better clinical efficacy in the treatment of advanced NSCLC patients with EGFR mutation-positive. It is reasonable to speculate that YYJD may also have the effect of reducing toxicity and increasing the efficiency of osimertinib.

Qi and Yin deficiency syndrome is one of the most common deficiency syndromes in TCM, manifesting as a pathological state in which both qi and yin deficiency coexist. The typical symptoms are cough, less sputum, fatigue, shortness of breath, dry mouth with less drinking, spontaneous sweating, reddish tongue, or tongue with teeth imprints, thready and weak pulse (Zheng, 2002). Meanwhile, the types of TCM syndromes under EGFR mutations in lung adenocarcinoma are dominated by Qi and Yin deficiency syndrome, and treatment should pay attention to tonifying Qi and nourishing Yin (Wang and Xu, 2017). YYJD is a CHM compound based on TCM theory that mainly exerts the effects of tonifying Qi, nourishing Yin, and detoxifying. In the subgroup analysis of the CATLA study, we found that YYJD had a better clinical benefit for advanced NSCLC patients with EGFR-sensitive mutations, extending median PFS by 16.26 months (Jiao et al., 2019). In addition, most trials have shown that the combination of EGFR-TKIs with oral CHM that tonifies Qi and/or nourishes Yin significantly delays acquired resistance while increasing the ORR of EGFR-TKIs (Lu et al., 2021). Therefore, in the design of this study, the intervention was set as YYJD with greater clinical benefit in order to minimize the impact of TCM syndrome differentiation on outcomes.

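### The sample of 314 does not follow from its own inputs: with exponential PFS, 18 versus 23 months needs about 523 events for 80% power, and 314 patients give about 31% power on the stated timeline

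*Protocol article*

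**What the plan says.** The Sample Size section states that "PFS is the primary endpoint" and that "the median PFS of the control group is expected to be 18 months and that of the intervention group is expected to be 23 months". Patients are to be recruited over 18 months, and the whole trial is to last 30. Allocation is 1:1, alpha 0.05, beta 0.20 and average censoring 1% per month. The result, from PASS 14, is that "the total sample size is 314 cases, 157 cases in each group". The section gives no hazard ratio, survival distribution or target number of events. Statistical Analysis fixes two-tailed testing at 0.05 and the log-rank test for PFS.

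Two other places bear on the inputs:

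- **Recruitment period.** Trial Status gives January 2021 to December 2022, about 24 months rather than 18.
- **Source of the medians.** Sample Size credits them to the group's previous study. The Introduction and Discussion say that study used gefitinib, erlotinib or icotinib. Of it and similar trials the Introduction says "These trials mainly involve first-generation EGFR-TKIs", and the Discussion reports of it that "The median PFS was prolonged by 5 months as first-line treatment". For osimertinib, the Discussion gives a median PFS of 18 months from a cited external trial, while the Introduction says that "acquired resistance to osimertinib develops over a median of 18.9 months".

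**The concern.** A difference of 18 versus 23 months is a modest effect on the hazard scale, and 314 patients looked too few to detect it with 80% power after 12 to 30 months of follow-up. Inputs and output stand in the same paragraph, so the gap is not a detail left to a statistical analysis plan.

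This is the only power statement, and it concerns the primary endpoint. If the herbal decoction really adds five months and power is near 31%, the trial will miss the effect about two times in three. A reader who believes the stated 80% would then take a non-significant result as fairly strong evidence of no benefit.

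**Working it through.** **Inputs.** From Sample Size: medians 18 and 23 months, accrual 18 months, total 30 months, 1:1, alpha 0.05, power 0.80, censoring 1% per month, N = 314. From Statistical Analysis: two-sided log-rank test. Assumed, because not stated: exponential PFS and uniform accrual.

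**1. Required events (Schoenfeld).** HR = 18/23 = 0.783, ln HR = −0.2451.

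d = 4 × (1.960 + 0.842)² / 0.2451² ≈ 523. One-sided 0.05 gives 412. Freedman's formula gives 528 and 416. All exceed 314.

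**2. Ceiling.** If all 314 patients had an event: √314 × 0.2451/2 − 1.960 = 0.212, power 58% (70% one-sided). At this hazard ratio no accrual pattern or length of follow-up reaches 80%.

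**3. Events at month 30.** With λ = ln 2/median, c = −ln 0.99 = 0.01005 and L = λ + c:

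p = (λ/L) × [1 − (e^(−12L) − e^(−30L))/(18L)]

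- Control: λ = 0.03851, L = 0.04856, p = 0.793 × [1 − (0.5584 − 0.2330)/0.8741] = 0.498
- Intervention: λ = 0.03014, L = 0.04019, p = 0.750 × [1 − (0.6174 − 0.2995)/0.7234] = 0.420

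Events = 157 × (0.498 + 0.420) ≈ 144.

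**4. Power.** √144.2 × 0.2451/2 − 1.960 = −0.488, so power = 31%. A 10,000-run log-rank simulation gave 31.0% with 144.3 events on average.

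**5. N for 80% power.** 523/0.459 ≈ 1,140.

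**6. Attempts to reproduce 314.**

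| Reading | N for 80% power |
|---|---|
| As stated, two-sided (Schoenfeld / Freedman) | 1,139 / 1,150 |
| Lachin-Foulkes, two-sided | 1,147 |
| One-sided 0.05 | 897 |
| No censoring, two-sided | 1,038 |
| 30 months added after accrual, two-sided / one-sided | 830 / 654 |

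None comes near 314.

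**7. Recruitment period in Trial Status.** With 24 months of accrual and 30 in total, p = 0.443 and 0.372. Events = 157 × 0.815 = 128, and √128 × 0.2451/2 − 1.960 = −0.573, power 28%. If the total is extended to 36 months, about 155 events and 33%.

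**8. Effect detectable with 80% power.** On the Sample Size timeline, a 29.3-month intervention median gives HR = 18/29.3 = 0.614 and p = 0.351. Events = 157 × (0.498 + 0.351) ≈ 133, and √133 × 0.487/2 − 1.960 = 0.85, power 80%. The events must be recalculated for each effect. Holding them at 144 suggests HR 0.63 (28.7 months), but at 28.7 months only about 134 events occur and power is 77%.

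**9. Precision.** With 144 events, an observed HR of 0.783 has 95% limits exp(−0.2451 ± 1.96 × 2/√144.2) = 0.56 to 1.08.

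**The case against.** **The distribution is unstated.** This is the strongest objection. Medians alone do not fix a hazard ratio. Under Weibull PFS with a rising hazard, the same medians and timeline give about 42% power at shape 1.2, 59% at 1.5, 75% at 1.8 and 83% at 2.0. A shape of about 1.9 to 2 would rescue the paragraph. The objection stands to this extent: the 31% is conditional on exponential PFS and should be labelled so. It does not save the text, which states no rising hazard; a calculation resting on one would have to say so.

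**An input may be misprinted.** The article condenses a fuller protocol, so a median or duration could have been copied wrongly. The documents cannot settle this, which is why checking the software inputs comes first.

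**Two stronger readings are not supported.**

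- A reader might infer that the 18-month control median has no basis, since the previous study did not use osimertinib. The Discussion itself gives 18 months for osimertinib from an external trial. What remains is a misattributed source, a minor point.
- A reader might infer that 314 was calculated for first-generation drugs, because 10 versus 15 months gives N of about 305. But 9 versus 14 gives 246 and 11 versus 16 gives 373, and the previous study's control median is not in the article. The match is conjecture.

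**Conclusion.** The point holds. The step from inputs to 314 is wrong as written. The firmest part needs only HR 0.783, which follows from exponential PFS: the required events (523, or 412 one-sided) exceed the number of patients, so 80% power is out of reach however long follow-up lasts.

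The size of the shortfall also rests on uniform accrual: about 31% on the Sample Size timeline and about 28% with 24 months of recruitment and 30 in total. Uniform accrual may be generous. Trial Status reports 58 patients by 23 December 2021, which is 58/314 = 18% of the target after about half of the 24 months; later entry means fewer events by month 30.

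The documents do not support saying that power is 31% whatever the distribution, nor that the 18-month control assumption is itself mistaken.

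**What to change.** 1. Check the sample-size software inputs and output against the Sample Size section.
2. Reconcile the recruitment period there (18 months) with Trial Status (about 24 months), and state the total duration that follows.
3. If the inputs stand, rewrite the paragraph to give the assumed hazard ratio and survival distribution, the expected PFS events on the reconciled timeline, the actual power for 18 versus 23 months (about 28 to 31%) and the effect detectable with 80% power (HR about 0.61 on the 18-month recruitment timeline, to be recalculated if that changes).
4. Correct the source of the control median. The previous study can be cited for the five-month gain on first-generation drugs, but not for an osimertinib median.
5. State in the analysis section that a non-significant result does not exclude HR 0.78 and will be interpreted through the hazard ratio and its 95% confidence interval.

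This is a change of wording in the protocol, the analysis plan and the registry entry. It needs no extra enrolment and no unblinding, and it should be made before results are known. The cost is a much less favourable published power figure.

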### Randomization

Eligible patients enrolled at each site will be randomly allocated to either the O+YYJD group or the O+placebo group at a 1:1 ratio through a dynamic random method. When patient gender (male vs. female), age (≥65 years old vs. <65 years old), and enrollment center is input as stratified factors, the software will automatically output the results of randomization. Personnel for drug administration will be able to obtain a random number and group allocation immediately in the form of a short message service and complete drug distribution according to the allocation.

### Blinding

The randomization results and blinding codes will be kept strictly confidential. They will be concealed until interventions are all assigned and enrollment, follow-up, data collection, data cleaning, and analysis are completed. Participants and researchers, including paramedics, investigators, outcomes assessors, and statisticians, will be unaware of the allocation.

### Interventions

Patients in the O+YYJD group will receive osimertinib and YYJD granule. Patients in the O+placebo group will receive osimertinib and placebo.

#### Yiqi-Yangyin-Jiedu Decoction

YYJD is produced into granules by Tianjiang Pharmaceutical Co., Ltd. (Jiangyin, Jiangsu Province, China) as previously reported (Wang et al., 2018) and the composition of YYJD is shown in Table 1. YYJD granules are taken with 150 ml of warm water twice a day after breakfast and lunch.

**TABLE 1 T1:** Composition of Yiqi-Yangyin-Jiedu decoction.

Drug name	Produced from	Dosage (g)
*Astragalus mongholicus* Bunge [Fabaceae]	Dry rhizoma	30
*Codonopsis pilosula* (Franch.) Nannf. [Campanulaceae]	Dry rhizoma	9
*Atractylodes macrocephala* Koidz. [Asteraceae]	Dry rhizoma	12
*Poria cocos* (Schw.) Wolf. [Polyporaceae]	Dry sclerotia	15
*Epimedium brevicornu* Maxim. [Berberidaceae]	Herbal	15
*Trigonella foenum-graecum* L. [Fabaceae]	Dry seed	15
*Cullen corylifolium* (L.) Medik. [Fabaceae]	Fruit	12
*Adenophora stricta* Miq. [Campanulaceae]	Dry rhizoma	30
*Glehnia littoralis* (A.Gray) F.Schmidt ex Miq. [Apiaceae]	Dry rhizoma	30
*Asparagus cochinchinensis* (Lour.) Merr. [Asparagaceae]	Dry rhizoma	15
*Ophiopogon japonicus* (Thunb.) Ker Gawl. [Asparagaceae]	Dry rhizoma	15
*Lilium brownii* var. *viridulum* Baker [Liliaceae]	Scale leaf	15
*Ligustrum lucidum* W.T.Aiton [Oleaceae]	Fruit	12
*Prunella vulgaris* L. [Lamiaceae]	Dry spikes	7.5
*Arisaema heterophyllum* Blume [Araceae]	Dry rhizoma	15
*Amorphophallus konjac* K.Koch [Araceae]	Dry tubers	15
*Cremastra appendiculata* (D.Don) Makino [Orchidaceae]	Dry pseudobulb	7.5
*Euphorbia helioscopia* L. [Euphorbiaceae]	Herbal	7.5
*Selaginella doederleinii* Hieron. [Selaginellaceae]	Herbal	15
*Salvia chinensis* Benth. [Lamiaceae]	Herbal	15
*Paris polyphylla* var. *chinensis* (Franch.) H.Hara [Melanthiaceae]	Dry rhizoma	7.5
*Ziziphus jujuba* Mill. [Rhamnaceae]	Fruit	4.5

#### Placebo

Placebo is produced into granules by Tianjiang Pharmaceutical Co., Ltd. (Jiangyin, Jiangsu Province, China) with the most similar package, color, smell, and shape to YYJD but without medical ingredients. It is taken with 150 ml of warm water twice a day after breakfast and lunch.

#### Osimertinib

Osimertinib (TAGRISSO, AstraZeneca, United Kingdom) should be taken at 80 mg per day. Patients enrolled in this study should continue intervention until disease progression or intolerable adverse effects.

### Outcomes

Computed tomography (CT) or magnetic resonance (MR) imaging will be used to assess the tumor at baseline, 4 weeks after treatment, and every 8 weeks afterward until disease progression or death. Objective response is evaluated according to RECIST 1.1, established by the National Cancer Institute (NCI), and divided into the following four situations: Complete Response (CR), Partial Response (PR), Stable Disease (SD), and Progressive Disease (PD).

#### Primary Outcome

PFS: measured with the date of the videography from a random assignment to the date of objective progression or death by the researcher.

#### Secondary Outcomes

(1) Overall survival (OS): calculated as the time from randomization to death due to any cause. For subjects who are lost to follow-up before death, the time of the last follow-up is used as the time of no death.(2) Objective response rate (ORR): calculated based on the effective rate of CR+PR patients.(3) Disease control rate (DCR): calculated based on the effective rate of CR+PR+SD patients.(4) Physical condition: assessed following the ECOG PS standard at the same time point of image evaluation.(5) QoL: evaluated with Functional Assessment of Cancer Therapy-Lung (FACT-L) questionnaire, Lung Cancer Symptom Scale (LCSS) and TCM syndrome score at the same time point of image evaluation. TCM syndrome score will be evaluated based on the grading scales of lung cancer symptoms required in the Guiding Principles of Clinical Research of New Chinese Medicine Treating Primary Bronchial Lung Cancer (2002 Edition) issued by the National Medical Products Administration of China.(6) Safety assessments: Participants will be asked and all adverse events (AEs) during treatment will be recorded at each visit, and all AEs reported will be analyzed. Blood, urine, and stool routine, liver function, and kidney function are tested for adverse reactions at the same time point of image evaluation and evaluated according to common terminology criteria for adverse events (CTCAE) version 5.0 (https://ctep.cancer.gov).

### Participant Timeline

The schedule of enrolment, interventions, and assessments is as shown in Figure 2.

**FIGURE 2 F2:**
[figure not shown]
The schedule of enrolment, interventions, and assessments.

### Data Collection and Management

The data will be collected with the use of paper case report forms (CRF) by researchers from each center. Participants will be given a separate space to fill out the QoL form for privacy concerns. The data management specialist of each center will use the electronic data capture (EDC) system for data entry and management. The system will verify the entered data, and the questionable data will be confirmed or corrected by researchers after re-checking. The researchers responsible for data analysis can access the data only after the patient recruitment is completed. The sub-center will conduct a self-inspection every month, the main center will conduct an inspection of the sub-center every 3 months, and the competent unit of the study will conduct a project verification once every 6 months. Relevant researchers will need to reply and rectify any problems found within 2 weeks.

### Quality Control

All researchers will receive unified training so that they have a full understanding of clinical trials before the start of the trial. In order to improve patients’ compliance with osimertinib, we will provide detailed information on the benefits of using osimertinib as first-line treatment compared with first-generation EGFR-TKIs and inform patients that the first-line treatment of osimertinib for advanced non-small cell lung cancer with EGFR mutation-positive (Ex19del or L858R) can be reimbursed by medical insurance in China. This makes the financial burden caused by osimertinib relatively small and valuable.

### Statistical Analysis

Data analysis will follow the trial’s statistical analysis plan. All data will be processed by statistical analysis with SAS 9.4 software analysis. Two-tailed *p* values <0.05 are considered statistically significant. The analysis will follow intention-to-treat, full analysis set, and per-protocol subject principles for the evaluation of primary and secondary outcomes. The safety data set that includes all subjects who received at least one treatment after randomization will be used to evaluate safety and tolerance. Missing data will be processed with the multiple imputation method.

The baseline characteristics will be reported according to treatment groups. PFS and OS will be illustrated by the Kaplan–Meier survival curve and compared between groups using the log-rank test. The secondary outcomes will be summarized with frequency, mean, standard deviation, median, and range. At each time point, comparisons between the experimental group and the placebo group will be conducted using the Group t-test or Wilcoxon rank-sum test (for measurement data) and the rank-sum test and CMH test (for count data). Fisher’s exact test will be used to compare tumor response rates between the arms. For PFS, an adjusted Cox regression model will be used to estimate the adjusted HRs for differences between the treatment arms with the selected prognostic factors, including the center, EGFR mutation type, age, sex, EGFR-TKI drugs, smoking status, and ECOG PS.

Safety will be documented in adverse event forms and presented with descriptive statistics for each group. The frequency difference of adverse events between groups will be assessed by the chi-square test or Fisher’s exact test. For different AE severities, a rank-sum test will be performed to analyze the independent ordered multiple category data between the two groups.

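### The PFS, OS and response tests are named without the factors used in allocation (a small loss of efficiency, not of validity), and the adjusted PFS model lists a TKI covariate that is constant in this trial

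*Protocol article*

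**What the plan says.** - **Allocation.** The Randomization section assigns patients "at a 1:1 ratio through a dynamic random method". The inputs are given as "When patient gender (male vs. female), age (≥65 years old vs. <65 years old), and enrollment center is input as stratified factors".
- **Primary endpoint.** The Sample Size section states that "PFS is the primary endpoint".
- **Tests.** In the Statistical Analysis section, PFS and OS are "compared between groups using the log-rank test", with no stratification mentioned. Fisher's exact test "will be used to compare tumor response rates between the arms".
- **Adjusted model.** The same section plans a Cox model, for PFS only, with prognostic factors "including the center, EGFR mutation type, age, sex, EGFR-TKI drugs, smoking status, and ECOG PS".
- **Treatment.** The Interventions section gives osimertinib to both arms. For the control arm it reads: "Patients in the O+placebo group will receive osimertinib and placebo". Inclusion criterion 4 rules out earlier treatment for locally advanced or metastatic disease.

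**The concern.** Two things do not fit together.

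First, the sponsor balances the arms on sex, age group and centre, and itself lists these three among the prognostic factors for PFS. The tests as named do not use them. For PFS the adjusted Cox model does, so the mismatch there is confined to the test. For OS, ORR and DCR no stated analysis uses them. When arms are balanced on a factor that truly predicts outcome, a test that ignores it tends to be slightly conservative and a little less powerful.

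Second, the Cox covariate list contains the EGFR-TKI drug. That factor varied in the earlier CATLA trial (gefitinib, erlotinib or icotinib), but here every patient takes osimertinib. A carry-over from the earlier trial is plausible, though that is an inference. The item contradicts the design whatever its origin.

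**Working it through.** **Plan figure.** The article attaches no number to the choice of test, so there is none to reproduce on this point. The design inputs from the Sample Size section set the scene: 314 patients, medians of 18 and 23 months, 18 months of recruitment, 30 months in total, 1% censoring per month.

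**Expected events.** Assume exponential PFS and uniform accrual, with λ = ln 2 / median, δ = −ln 0.99 = 0.01005 and g = λ + δ. The event probability is

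p = (λ/g) × [1 − (e^(−12g) − e^(−30g)) / (18g)].

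- Control: λ = 0.0385, g = 0.0486, p = 0.498.
- Intervention (median 23 months): p = 0.420.
- Mean 0.459 × 314 ≈ 144 events.

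Four strata (sex × age group) give 144/4 = 36 events each on average. Crossing with 8 centres gives 32 strata and 144/32 = 4.5 events each.

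**Simulation.** 3,000 trials per setting, N = 314, accrual and censoring as above, two-sided 5%. Assumptions not in the article:

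- minimisation with a biased-coin probability of 0.8;
- half the patients of each sex, 40% aged 65 or over, 8 centres of equal expected size;
- moderate prognostic effects: HR 1.35 for sex, 1.2 for age, centre range 1.5;
- strong prognostic effects: HR 1.8 for sex, 1.5 for age, centre range 2.5.

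The planned effect is 18/23 = 0.783. An HR of 0.65 is added for comparison. Entries are the percentage of trials rejecting.

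| Prognostic effects | True HR | No strata | Sex × age (4) | With centre (32) |
|---|---|---|---|---|
| none | 1 | 5.3 | 5.0 | 5.1 |
| moderate | 1 | 4.9 | 5.1 | 5.6 |
| strong | 1 | 4.4 | 5.0 | 5.2 |
| none | 0.783 | 30.3 | 30.1 | 25.8 |
| moderate | 0.783 | 29.3 | 29.7 | 26.1 |
| strong | 0.783 | 26.2 | 28.2 | 26.8 |
| none | 0.65 | 72.4 | 71.0 | 63.1 |
| moderate | 0.65 | 70.1 | 70.0 | 63.7 |
| strong | 0.65 | 68.2 | 70.3 | 64.8 |

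The simulation standard error is √(0.05 × 0.95/3000) ≈ 0.4 points for type I error and √(0.30 × 0.70/3000) ≈ 0.8 points for power near 30%.

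- **Validity.** The test without strata rejects in 4.4% to 5.3% of null trials. The lowest value is (5.0 − 4.4)/0.4 = 1.5 standard errors below 5%, so even the conservatism is slight.
- **Gain from 4 strata.** At the planned effect: −0.2, +0.4 and +2.0 points. At HR 0.65: −1.4, −0.1 and +2.1 points. If neither factor is prognostic there is nothing to gain, and up to about a point may be lost.
- **Cost of 32 strata against 4, at the planned effect.** With no or moderate prognostic effects: 30.1 − 25.8 = 4.3 and 29.7 − 26.1 = 3.6 points. At HR 0.65 the cost is larger, at 5.5 to 7.9 points.

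A second simulation, with two balanced binary factors and a treatment HR of 0.63, agrees. Power without and with strata was 74.3% and 76.5% at a log-HR of 0.5 per factor, and 76.2% and 76.1% at 0.3. Type I error was 4.5% to 5.4%.

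Power near 30% at the planned effect reflects a separate problem with the sample size. Only the differences between columns matter here.

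**Constant covariate.** In the Cox partial likelihood, a covariate contributes its value minus its risk-set mean at each event. If every patient has the same value, each contribution is 0 and so is the information. A fit with treatment plus a constant column gave the Hessian [[−36.75, 0], [0, 0]], of rank 1 out of 2. The coefficient of the constant term is not identified. The treatment row does not involve it, so the treatment HR is unchanged.

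**The case against.** The strongest reply is that stratification of the test belongs in the SAP, which the article says will govern the analysis and which is not shown. The article does not say that the test is unstratified. The PFS Cox model already carries all three allocation factors, a log-rank test without strata is a legitimate choice, and the gain depends on prognostic strengths that no document supplies. Fisher's exact test for response is likewise valid.

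Most of this stands, and it limits the weight of the first part. That part is an inexpensive improvement to the analysis as the article words it, and an unseen SAP may already have made it. The reply does not reach the second part. Listing a covariate that the design holds constant is a positive statement that needs correcting.

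A reader might infer more than the documents support:

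- *That the primary test is invalid or biased.* Type I error stays at or slightly below the nominal level. Marginal and covariate-adjusted hazard ratios are different quantities, so a gap between them is not an error, and the log-rank test itself reports no hazard ratio.
- *That the adjusted model cannot be fitted.* One coefficient cannot be estimated; the rest of the model can.
- *That the TKI term means treatment received after randomisation.* The article calls these covariates prognostic factors, and nothing in it suggests later therapy. That reading should still be ruled out, because it would condition the treatment effect on a post-randomisation variable.

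**Conclusion.** The point holds in two modest parts.

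1. **Tests without allocation factors.** As worded, the tests for PFS, OS and response do not use the factors on which allocation is balanced. For PFS only the adjusted Cox model does. The log-rank test is valid and at most slightly conservative. The loss is about 0 to 2 points of power if sex and age are prognostic, resting on the assumed strengths and the simulation set-up above. OS and response were not simulated, so no size is claimed for them.
2. **Constant TKI covariate.** This is certain from the text and needs no assumption beyond the design being followed. It leaves the treatment hazard ratio unaffected, so it is a correction to the specification and not a threat to the result.

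**What to change.** - **PFS test.** Make the primary test a log-rank test stratified by sex and age group (65 or over against under 65), giving 4 strata. Do not cross these with centre.
- **PFS estimate.** Report the main hazard ratio from the Cox model already planned, which handles centre as a covariate, and state that the stratified log-rank test decides significance.
- **OS.** Use the same stratified test and adjusted model.
- **ORR and DCR.** Use a CMH test stratified by sex and age group. The article already names CMH for count data.
- **Cox covariates.** Delete the EGFR-TKI drug term. It needs no replacement and must not be redefined as a TKI given after randomisation.

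The cost is wording in the SAP, settled before unblinding. Sex, age group and centre are entered at randomisation, so no new data are needed. If the SAP already stratifies the test, only the covariate deletion remains.
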